#### Statistical Analyses

Our sample size was calculated based on our previous work involving PET imaging in PD in which participants were randomized into either gene therapy or sham-surgery groups, and assessed at 6 months follow-up (Ko et al., 2014a). With anticipated ρ2 = 0.673 [20% more than what is expected for placebo effect-related pattern’s explanation of clinical benefits induced by sham surgery over 6-months (Ko et al., 2014a)], G^∗^Power (version 3.1.9.2; RRID:SCR_013726) estimates the minimal sample size to be 12 (effect size f2 = 2.060). With maximally anticipated drop-out rate of 10% (e.g., motion artifacts, patient’s voluntary withdrawal, etc.); we require 13 subjects per group/site.

MATLAB (The Math Works Inc., Natick, MA, United States version 2010a) will be used to compute the outcome measures. Normality of the data will be assessed using the Shapiro-Wilks test. Sphericity will be assessed using Mauchly’s test. For normally distributed data sets, a mixed-model ANOVA will be used to examine the effects of time (pre– and post-intervention), group (XG and CG) and interaction of time^∗^group of all behavioral outcome measures (gait, cognitive, neuropsychological, fall rates, physical activity levels, and health-related quality of life). Note the time factor for fall rates, physical activity outcome measures, and health-related quality of life will include the 6-month and 12-month follow-up time periods. Non-normally distributed data will be assessed using the Wilcoxon-Signed rank test to determine differences between pre- and post-intervention. The significance level will be set at *p* < 0.05, and statistical analysis will be conducted using SPSS (v.22; SPSS Science, Chicago, IL, United States).

For the neuroimaging data, Aim 1 will use PET data to compare levels of metabolic activity by region between; (a) single-walk only and DT-walk trials, and (b) PD and able-bodied age-matched controls. Aim 2 will use PET and MRI (RS-fMRI, pCASL, and DTI) data to investigate neural changes (whole-brain and ROIs) between pre- and post-intervention. See Table 1 for the ROIs to be used in the PET and RS-fMRI data for Aims 1 and 2. Paired sample *t*-tests will be conducted for these different neuroimaging modalities, with age and gender included as regressors of no interest. Additional correlational analyses are planned to investigate the relationship between changes in neural activity and behavioral metrics such as cognitive task performance and gait measures.

**TABLE 1 T1:** Regions of interest for the PET and fMRI ROI analyses.

**Amygdala, L**	**Dorsolateral PFC, L**	**Inferior Temporal, R**	**Mesial Temporal, L**	**Orbital frontal, R**	**Thalamus, R**
Amygdala, R	Dorsolateral PFC, R	Insula, L	Mesial Temporal, R	Putamen, L	Uncus, L
Anterior Cingulate, L	Frontal pole, L	Insula, R	Midbrain	Putamen, R	Uncus, R
Anterior Cingulate, R	Frontal pole, R	Lateral Temporal, L	Middle Temporal, L	Substantia nigra	Ventral Striatum, L
Subgenual cingulate (BA 25)	Hippocampus, L	Lateral Temporal, R	Middle Temporal, R	Superior Temporal, L	Ventral Striatum, R
Caudate, L	Hippocampus, R	Medial PFC, L	Occipital	Superior Temporal, R	Ventrolateral PFC, L
Caudate, R	Inferior Temporal, L	Medial PFC, R	Orbital frontal, L	Thalamus, L	Ventrolateral PFC, R

*L, left; R, right; PFC, prefrontal cortex.*

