##### FDG-PET Analysis

For FDG-PET data, an in-house whole-brain mask will be used as the explicit mask. PET images will be proportionally scaled to each image’s global values for statistical analysis. For both walk only and DT-walking conditions FDG-PET, ordinal trend/canonical variate analysis [OrT/CVA (Habeck et al., 2005)] will be applied to characterize the normal DT-walking-related brain metabolic pattern (NDWP), by comparing FDG-PET of single-walking vs. DT-walking in the healthy controls. First, the OrT transforms the preprocessed image data to increase the salience of ordinal trend effects, allowing the proceeding principal component analysis (PCA) to identify principal components with targeted expression (i.e., a consistent increase of pattern expression at the individual subject level), while also controlling for the salience of untargeted expression (Habeck et al., 2005). The principal components that result from the OrT can either be used individually, or can be linearly combined, allowing the expression of a given metabolic pattern to be quantified in each scan. Similarly, the PD-specific DT-walking-related brain metabolic pattern (PDWP) will be produced (i.e., DT-walking vs. single-walking in PD patients at pre-intervention). Additionally, we will examine if there is a different metabolic pattern, specific to the 10-week treatment-induced clinical benefits in PD by OrT/CVA (post- vs. pre-intervention during DT-walking). The topographical rating scale of the proposed FDG-PET patterns (i.e., NDWP, PDWP, and longitudinal pattern) will be computed in each FDG-PET image. Furthermore, behavioral scores (such as gait and cognitive performance) will be correlated with changes in metabolic patterns from pre- to post-intervention. The topography of the resulting spatial patterns will be compared using similarity test correcting for auto-correlation (Ko et al., 2014b).

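### The treatment-related PET pattern is derived and tested post versus pre, with no stated comparison between the randomised arms, so it cannot be attributed to dual-task training

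*Protocol article*

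**What the plan says.** Objective 2(b) (Objectives) places the pattern of metabolic brain activity among the outcomes on which a randomised, two-arm trial will examine the effect of the training.

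The analysis text for PET is narrower:
- Statistical Analyses assigns Aim 2 imaging to changes between the pre- and post-intervention scans. It names paired-sample t-tests with age and gender as regressors, plus correlations with behaviour.
- FDG-PET Analysis will look for a further pattern "specific to the 10-week treatment-induced clinical benefits in PD by OrT/CVA (post- vs. pre-intervention during DT-walking"), score all patterns in each image, and adds that "behavioral scores (such as gait and cognitive performance) will be correlated with changes in metabolic patterns from pre- to post-intervention". It does not say whether the post-versus-pre derivation pools the arms or is done within one.

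For the behavioural outcomes, Statistical Analyses does specify a time-by-group term. Anticipated and Preliminary Results expects significant improvement in gait and cognition in both arms, larger in XG. It also states XG-versus-CG expectations for the resting-state fMRI and pCASL measures.

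The sample-size paragraph begins "With anticipated ρ2 = 0.673", sets that value as "20% more than what is expected for placebo effect-related pattern’s explanation of clinical benefits induced by sham surgery over 6-months", and G*Power then "estimates the minimal sample size to be 12 (effect size f2 = 2.060").

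**The concern.** Two features of the plan make a one-group, pre/post reading unsafe for a claim about treatment. First, if both arms improve, a post-versus-pre pattern can reflect treadmill practice, familiarity with the test games and scanner, expectation or time, as well as dual-task training. Participants know whether they play games while walking. Second, the article's own benchmark describes a PET pattern that explained a sizeable share of clinical benefit after an inactive procedure. By the plan's own reference, then, a strong link between pattern change and benefit is not evidence of an active treatment.

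At stake is the mechanistic conclusion of Aim 2. A significant pre/post pattern, or a correlation with better gait, could be reported as plasticity caused by dual-task training when nothing in the stated PET analysis separates it from non-specific improvement. The randomised comparison that could separate them is available but is not named for PET.

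**Working it through.** **1. What the sizing tests.** Inputs from Statistical Analyses: ρ2 = 0.673, f2 = 2.060, N = 12. The formula is f2 = ρ2/(1 − ρ2) = 0.673/0.327 = 2.058, which matches "effect size f2 = 2.060" to rounding. The effect size is therefore the whole ρ2 against a null of zero.

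**2. Reproducing N = 12.** I used the noncentral F test of R2 = 0 with λ = N·f2, degrees of freedom p and N − p − 1, and α = 0.05. The article states 0.05 for its analyses but does not tie it to the sizing, and gives neither the number of predictors p nor the power. N = 12 is the minimum for each of these:

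| p | target power | power at N = 12 |
|---|---|---|
| 1 | 99% | 0.994 |
| 2 | 95% | 0.968 |
| 3 | 90% | 0.913 |
| 4 | 80% | 0.826 |

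**3. The sham reference (assumption; not printed).** Relative reading: 0.673/1.2 = 0.561. Absolute reading: 0.673 − 0.20 = 0.473.

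**4. How often a sham-level association is significant against zero.** Same test, with the true ρ2 set to the reference:

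| true ρ2 | N | p = 1 | p = 2 | p = 3 | p = 4 |
|---|---|---|---|---|---|
| 0.561 | 12 | 94% | 84% | 73% | 61% |
| 0.473 | 12 | 84% | 69% | 57% | 45% |
| 0.561 | 24 | >99% | >99% | 99% | 98% |
| 0.473 | 24 | 99% | 98% | 96% | 92% |

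N = 24 is one arm over both sites (2 × 12). If predictors are treated as random, the N = 12 rates are lower: 86/76/65/54% and 76/62/51/41%. These are correct rejections of zero. They show only that rejecting zero does not tell a training effect from a sham-like response.

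**5. Precision.** For a simple correlation with an observed ρ2 of 0.673 and N = 12: r = 0.820, Fisher z = 1.158, SE = 1/√9 = 0.333. The 95% CI for ρ2 is about 0.22 to 0.90, which covers both reference values.

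**6. Stated contrasts side by side.**

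| Outcome | Contrast stated |
|---|---|
| Gait, cognition, other behaviour | time, group, time-by-group |
| Resting-state fMRI, pCASL | pre/post paired t-test; XG-versus-CG expectation in the anticipated results |
| PET pattern | post versus pre (OrT/CVA, paired t-test); correlation with behaviour |

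Only the PET row has no between-arm element, although objective 2(b) concerns the randomised training.

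**7. What the randomised contrast could show.** With 24 per arm, the SE of a standardised difference is √(2/24) = 0.289. The 95% half-width is about 1.96 × 0.289 = 0.57 SD, and the difference detectable with 80% power is about (1.96 + 0.84) × 0.289 = 0.81 SD. Here SD is that of the post score after baseline adjustment.

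**The case against.** **The sizing itself.** A reader might infer that the sample-size calculation is wrong because it ignores the sham benchmark, or that 12 patients are claimed to be enough to beat it. The text supports neither. The sham figure only explains where the anticipated value came from, and testing an anticipated effect against zero is ordinary practice. Nor is an incremental effect size a valid replacement, such as (0.673 − 0.561)/0.327 = 0.34 or 0.20/0.327 = 0.61. That formula needs nested predictors in one sample, and a historical R2 from another intervention is not a reduced model here.

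**The word 'specific'.** The sentence in FDG-PET Analysis asks whether a further pattern exists after the normal and PD patterns have been defined, and a similarity test of topographies follows. It can fairly be read as 'different in topography', and as exploratory. That stands: the article nowhere says that a correlation excludes a placebo response. But the same sentence calls the benefits treatment-induced, and the contrast it names cannot establish that.

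**Condensed article.** Scores are computed in every image, so in both arms, and a between-arm contrast may exist in the full protocol or analysis plan. This is the strongest objection. It does not dispose of the point, because the article does not stay silent: it names the PET contrast, and that contrast is post versus pre.

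**A slope comparison as the remedy.** Comparing the pattern-benefit slope between arms would not settle the matter. Slopes could be equal even if training caused all the change, since CG is also an active programme, and unequal slopes would not show a training effect. At 24 per arm, power to separate 0.673 from the sham value in a between-arm comparison of correlations is only about 9–17%.

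**Conclusion.** The concern holds for the PET analysis of Aim 2, not for the sample size. As stated, the treatment-related pattern rests on post-versus-pre contrasts and on correlations with behaviour, with no XG-versus-CG comparison. Given that both arms are expected to improve, and given the plan's own sham-surgery reference, neither result could be attributed to dual-task training.

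The size of the problem depends on three figures that the article does not print: the sham ρ2 (taken as 0.473 to 0.561), the number of predictors (1 to 4, the configurations that return N = 12 at 80–99% power) and the power. In that range a sham-level association would be significant against zero in 45–94% of trials with 12 patients, and in at least 92% with 24. Saying that it would pass most of the time fails at N = 12 for four predictors with the lower reference (45%; 41% with random predictors). The attribution problem does not depend on these rates, because it follows from the missing randomised contrast.

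The comparator is an active programme, so a between-arm difference would isolate the dual-task component rather than training as a whole.

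**What to change.** 1. In Statistical Analyses and FDG-PET Analysis, make the Aim 2 PET test the randomised comparison: regress the post-intervention pattern score on arm, adjusting for the pre-intervention score, sex and Hoehn and Yahr stage (the stratification factors). Report the XG-minus-CG difference with its 95% CI. This mirrors the time-by-group term already planned for behaviour. The PD pattern derived before the intervention suits this well, because its derivation cannot depend on arm. If the longitudinal pattern is scored in the same way, state that it was derived without using arm.
2. Keep the post-versus-pre OrT/CVA and paired t-tests as descriptions of change.
3. Report pattern-behaviour correlations, pooled or within arm, as exploratory associations that non-specific improvement could also produce. An arm-by-pattern-change interaction may be added, as exploratory only.
4. In the sample-size paragraph, one sentence is enough: N = 12 is for testing ρ2 against zero and does not size a test against the sham value.

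Cost: a few sentences and one regression on scans already planned, with no added patients or visits. The downside is imprecision. At about 24 per arm the 95% CI half-width is roughly 0.57 of the baseline-adjusted SD, so a moderate difference may be missed and the PET conclusion should be worded accordingly.

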### Participants

52 patients with PD [26 from Winnipeg, MB, Canada (site 1) and 26 from Toronto, ON, Canada (site 2)], and 15 age-matched healthy, able-bodied control subjects (site 1) will be recruited in a 2-year time period. The criteria used for recruitment of the patients will include; (a) diagnosis of PD according to United Kingdom brain bank criteria (Hughes et al., 1992), (b) stage II-III of PD according to the Hoehn and Yahr scale (Bhidayasiri and Tarsy, 2012), (c) age 50–75 years, (d) adequate vision to see required images on a standard computer monitor, (e) able to score 26 or greater on the Montréal cognitive assessment scale [MoCA (Marinus et al., 2011)], (f) on stable medications for the past 3 months, and (g) able to walk overground for 2 min without an aid or cane. The exclusion criteria for participation will include the following: (a) diagnosis of any psychiatric comorbidity or history of any other neurological disease other than PD, (b) any other medical condition limiting participant ability to walk on the treadmill, and (c) neuroimaging contraindications (i.e., claustrophobia, severe dyskinesia, diabetes, non-compatible metal implants, etc.). Healthy able-bodied adults with the same inclusion/exclusion criteria listed above except for diagnosis of PD will be recruited.

All responders to calls for participation will undergo a screening assessment. Ethics approval has been obtained from the institutional Human Research Ethics Boards. All volunteer participants will be asked to read and sign the informed consent form. The Clinical trial has been registered at ClinicalTrials.gov, identifier: NCT04415775.

Successfully screened PD participants will be randomized to the experimental intervention (XG) or an active control arm (CG). A computerized block randomization procedure will be implemented by an independent statistician. Randomization will be stratified by stage of the disease (Hoehn and Yahr stage II and III). To ensure similar representation of men and women, randomization will also be stratified by sex. Randomization will be achieved by having participants choose an opaque sealed envelope, each containing a group assignment.

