## Anticipated and Preliminary Results

The anticipated results of this study can be broken down by objective. First, in comparing if and how metabolic brain activity differs during single and DT-walking in PD patients, compared to able-bodied controls, we will likely observe increased activation of sensorimotor and cerebellar brain regions and decreased activation in the PFC of the PD patients. We hypothesize that these changes in brain activation patterns will be associated with decreased gait and cognitive performance measures and the magnitude of DT effects. Second, we hypothesize that both training programs will result in significant improvements in gate and cognitive function with medium to large effect sizes, and that the DT training program will result in significantly greater improvements in the XG compared to CG, also with medium to large effect sizes. It is hypothesized that the DT treadmill-training program will result in specific and significant changes of the DT gait-related abnormal brain metabolic pattern observed in Objective 1.

Our behavioral and PET hypotheses are supported by a recent feasibility study that we completed in which 15 PD patients (Hoehn and Yahr stages II-III) participated in a 10-week DT-treadmill gait training program using the VMT and VCG as described in the “Methods” section above (Mahana et al., 2021). Significant improvements in the majority of gait variables (average and COV of SL and SW) with medium to large effect sizes were observed following the intervention. This was the case for both walk-only and DT-walking assessments. There were also significant improvements in VMT and VCG outcome measures post-intervention with medium to large effect sizes. This was the case when tested while sitting and while treadmill walking. In addition, a qualitative analysis of the participant’s experiences revealed that the program was challenging and required a high degree of mental processing. The majority of participants reported that the games were engaging and they appreciated the variety of games used for the DT training. Also, to note 3 of the 15 participants did not like playing the games.

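### The sample size of 12 per group/site is derived for a PET pattern-versus-benefit regression; the XG-versus-CG comparison that the trial randomises for has no sizing, and 52 patients detect only about d = 0.8 (change-score scale)

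*Protocol article*

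**What the plan says.** All references are to the protocol article. The sample-size paragraph (Statistical Analyses) begins "With anticipated ρ2 = 0.673". It explains this value as "20% more than what is expected for placebo effect-related pattern’s explanation of clinical benefits induced by sham surgery over 6-months", taken from an earlier PET study that compared gene therapy with sham surgery. From it, G*Power "estimates the minimal sample size to be 12 (effect size f2 = 2.060"). After an allowance for drop-out of at most 10%, the paragraph ends "we require 13 subjects per group/site". The Participants section enrols "52 patients with PD [26 from Winnipeg, MB, Canada (site 1) and 26 from Toronto", which is 2 arms × 2 sites × 13.

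The second objective (Objectives) is a two-arm, parallel-group randomised trial. The behavioural outcomes are tested by a mixed-model ANOVA with time, group and their interaction (Statistical Analyses). Under Anticipated and Preliminary Results, the authors expect both programmes to bring improvement, and beyond that "significantly greater improvements in the XG compared to CG, also with medium to large effect sizes".

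**The concern.** An f² obtained from a squared correlation measures how much of one variable's variance is explained by others. It is not a difference between randomised arms. The sample-size text contains no XG-CG difference, no standard deviation and no power for that difference, yet the same article predicts a significant between-arm advantage. A reader would take 52 to be the number chosen to show that advantage.

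The interpretation of the result is at stake. The control arm is active (treadmill walking plus seated games) and is itself expected to improve. If the true XG advantage is medium rather than large, a non-significant interaction could be the more likely outcome, and it could be read as evidence that dual-task training adds nothing.

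A smaller matter is that 13 per cell does not quite keep the stated minimum of 12 at the stated drop-out.

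**Working it through.** **1. Reproducing the plan's figure.** Inputs from Statistical Analyses: ρ² = 0.673, f² = 2.060, n = 12.
- f² = ρ²/(1 − ρ²) = 0.673/0.327 = 2.058. The stated 2.060 corresponds to ρ² = 2.060/3.060 = 0.6732, so the two agree to rounding.
- The paragraph does not give the number of predictors or the power, and α = 0.05 is stated for the analyses rather than for the sizing ("The significance level will be set at *p* < 0.05"). With the overall F test (noncentral F, λ = f²·n, α = 0.05), 12 is the smallest n for 4 predictors at 80% power (0.826), 3 at 90% (0.913), 2 at 95% (0.968) or 1 at 99% (0.994).

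So 12 is reproducible as a regression sample size, although which of these settings was used cannot be told.

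**2. Which planned analyses it fits.**
- It fits the correlations between neural and behavioural change (Statistical Analyses), and the treatment-related metabolic pattern with its correlation with gait and cognitive scores (FDG-PET Analysis).
- It does not fit the time-by-group interaction.
- No analysis is stated to be run within one arm at one site, although the requirement is expressed per group/site.

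**3. What 52 patients give for XG versus CG.** With two time points, the interaction test is a two-sample t test on change scores. Assumptions: two-sided α = 0.05, 26 per arm enrolled, and 23 per arm after 10% loss (26 × 0.9 = 23.4). Medium and large are taken as d = 0.5 and 0.8; the article does not define them. Power comes from the noncentral t distribution with noncentrality d·√(n/2) and 2n − 2 degrees of freedom.

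| n per arm | Power, d = 0.5 | Power, d = 0.8 | d detectable at 80% power |
|---|---|---|---|
| 26 | 42% | 81% | 0.79 |
| 23 | 38% | 76% | 0.84 |

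Here d is in SDs of the change score. On that scale, d = 0.5 needs 64 completers per arm for 80% power.

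**4. Sensitivity to the scale of d.** If d is in raw-score SDs and the SD is equal at both times, the change-score effect is d/√(2(1 − r)), where r is the pre-post correlation. The article does not give r, so a range is shown for d = 0.5 and 26 per arm.

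| r | Change-score d | Power |
|---|---|---|
| 0.3 | 0.42 | 32% |
| 0.5 | 0.50 | 42% |
| 0.7 | 0.65 | 63% |
| 0.8 | 0.79 | 80% |

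**5. Drop-out step.** 12/0.9 = 13.33 and 12 × 1.1 = 13.2. Both round up to 14 and both round to the nearest integer as 13. At 10% loss, 13 × 0.9 = 11.7 per cell, and 52 × 0.9 = 46.8 in total against 4 × 12 = 48. Inflating the total gives 48/0.9 = 53.3, that is 54. Rounding up each of the four cells gives 56. One loss in 13 is 7.7%.

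**The case against.** The strongest reply is that sizing on a PET-benefit relation is legitimate here. Imaging of the neural basis is central to both aims, the article names no primary outcome, and pattern-benefit correlations are planned. That stands, and it narrows the point: the calculation matches a real analysis, but not the randomised comparison.

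A second reply is that low power for a medium effect depends on scale. That also stands. With a pre-post correlation of 0.8, a raw-score d of 0.5 has about 80% power, so the article does not establish that a medium effect would probably be missed. This is why the detectable effect has to be stated with its scale.

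Three stronger readings are tempting and not supported:
- **That the trial must enrol 56.** That figure comes only from rounding four cells up separately; inflating the total gives 54. No stated analysis needs 12 completers in each cell, and 28 per arm would raise power at d = 0.5 (change-score scale) only from 42% to 45%.
- **That the 13 proves a wrong drop-out formula.** Both formulas give 13 when rounded to the nearest integer, so the figure cannot tell them apart.
- **That the between-arm hypothesis must be reworded to expect only a large effect.** It is a scientific expectation and need not be trimmed to the available power. Disclosing the detectable effect is enough.

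The unstated power and predictor count are details that a condensed article may leave to the full protocol, and are not held against it.

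**Conclusion.** The point holds as a mismatch between the sizing and the randomised comparison. The 12 belongs to a regression of clinical benefit on a PET pattern, and the XG-versus-CG interaction has no sizing of its own. At two-sided 0.05 and 80% power, 52 patients detect d of about 0.79 with no loss and about 0.84 with 10% loss, in change-score SDs. Power at d = 0.5 on that scale is 42% and 38%. On the raw-score scale, with 26 per arm, it is about 32% to 80% for r from 0.3 to 0.8.

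These figures assume a two-sample comparison of change scores over two time points and the usual meaning of medium and large. A null between-arm result should be read against the detectable effect and not as evidence of no benefit.

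The 13-versus-14 matter is a rounding shortfall of 0.3 of a patient per cell: true, but minor.

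**What to change.** Keep 52 patients and revise the sample-size paragraph:

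1. Say that the 12 applies to the regression of clinical benefit on the PET pattern, and not to XG versus CG.
2. Add the between-arm effect that 52 patients can detect: d of about 0.79 (26 per arm) or 0.84 (23 per arm) in change-score SDs at two-sided 0.05 and 80% power, with 42% and 38% power at d = 0.5. State the scale. If raw-score SDs are preferred, give the assumed pre-post correlation and a range around it.
3. Say that a non-significant XG-CG result will be interpreted against that detectable effect.
4. Restate the drop-out allowance: 13 per cell tolerates one loss (7.7%). Alternatively, give 14 as the figure strictly rounded up for 10%, with a note that 13 are enrolled.

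The cost is a few sentences. No extra patients are needed, and neither the hypothesis nor the analysis changes. The drawback is that the published figures look less favourable for the behavioural comparison.

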## Discussion

An integrated approach to treatment with embedded assessment of balance, gait, visuomotor, and cognition has the potential to impact both the prevention and rehabilitation of mobility limitations, and in cognitive function. Improved mobility functioning in PD directly translates to improved community ambulation, as well as increased physical activity and social participation. These benefits are known to have a significant preventative and disease-modifying impact.

New telerehabilitation technologies will likely improve clinical outcomes by making therapy more available, more motivating, and more specific and effective. While one of the pitfalls of the present study includes possible patient attrition, previous pilot-testing work showed high retention of participants, partly due to the engaging nature and low-level of adverse events related to the intervention (Mahana et al., 2021). The computerized DT platform presented in this study broadens the type of standardized visuomotor and executive cognitive activities for use for DT balance-gait training that has previously been reported. A comprehensive analysis of spatial and temporal features of steady state gait has a greater validity to measure gait performance (rhythm, pacing, and stability) as compared to gait speed alone. The use of interactive digital media provides a flexible method to produce a wide range of executive cognitive activities while performing complex motor behaviors such as walking. The types and amount of cognitive stimulation participants engage in during intervention needs to be objectively measured, and this will help clarify the potential added benefit of activities beyond physical exercise alone. Quantification of cognitive-motor interactions has the potential to be a valid non-invasive biomarker for early detection of balance-mobility limitations and cognitive decline in the early stage of disease, and with aging, although these results will not be generalizable to later stages of PD. Although participant motion is a potential pitfall for the neuroimaging data, only early-stage PD patients with controlled tremor will be recruited. Outcomes of this research will provide new insights into brain plasticity mechanisms and will accelerate further optimization and commercialization of multi-modal mobility-cognitive training applications along with accompanying smart electronic monitoring tools.

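### For fall rates, physical activity and quality of life, a classical repeated-measures ANOVA extended to 12 months by default drops anyone with a missing time level and discards their earlier data

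*Protocol article*

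**What the plan says.** The Statistical Analyses section of the protocol article states: "For normally distributed data sets, a mixed-model ANOVA will be used to examine the effects of time", with group and the time-by-group interaction as the other effects. It also states: "Sphericity will be assessed using Mauchly’s test". The software is SPSS v.22. For most behavioural outcomes time has two levels, before and after the intervention. For three outcome groups it is longer: "Note the time factor for fall rates, physical activity outcome measures, and health-related quality of life will include the 6-month and 12-month follow-up time periods". Data that are not normally distributed go instead to a Wilcoxon signed-rank test of pre against post.

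The same section allows for at most 10% drop-out, within a sample size calculation based on an earlier PET study. The Discussion says that "one of the pitfalls of the present study includes possible patient attrition", and the same sentence goes on to report high retention in pilot work.

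On data collection, the Figure 1 legend, Behavioral Testing and Neuropsychological Tests place behavioural and quality-of-life assessment at baseline, after the programme and at 6 months. Neuropsychological Tests has falls recorded for a year after the programme, by calendar. Physical Activity Tracking starts in week 2 of the programme and relies on weekly transfer of watch data by the participant.

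**The concern.** Mauchly's test belongs to the classical repeated-measures ANOVA. A likelihood-based mixed model with unstructured covariance has no use for it. In the model as stated it also has nothing to test when time has only two levels, so it matters exactly for the outcomes with follow-up levels. The classical procedure needs a complete row per participant and by default deletes any row with a gap.

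Someone who completes training and the 6-month period but leaves at month 8 would therefore drop out of the whole test for an outcome with a 12-month level, including the levels already observed. For falls, eight months of calendar data would go unused. The three outcome groups concerned are those followed longest, and two of them depend on what participants themselves record or transmit over a year. At stake are precision and, if leaving is related to outcome differently in the two arms, the validity of the group comparison.

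**Working it through.** **Inputs from the article.** 52 participants with PD; 13 per group and site over two groups and two sites, hence 26 per arm; stated maximum drop-out 10%; a minimum of 12 before drop-out, with f² = 2.060 from ρ² = 0.673.

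**The plan's own figure.** f² = 0.673/(1 − 0.673) = 2.058, which agrees with 2.060 up to rounding. A minimum of 12 is attainable under several combinations of power and number of predictors (for example 3 predictors at 90% power), neither of which the article states. Allowing for drop-out, 12 × 1.1 = 13.2 and 12/0.9 = 13.3, against the stated 13 (13 × 0.9 = 11.7). 13 × 4 = 52. The 10% is not tied to a time point, and one of its examples is an imaging artefact.

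**Loss at the stated 10%.** 52 × 0.9 = 46.8 complete, so about 5 of 52 are removed. If all of them leave after the post-training assessment, the immediate contrast uses 0.9n instead of n: SE ratio = 1/√0.9 = 1.05. If some leave earlier, the ratio is smaller. So 5% is the upper bound.

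**Loss under assumed rates per phase** (training; to 6 months; to 12 months). With loss q per phase, 26(1 − q) per arm have post-training data and 26(1 − q)³ are complete. SE ratio = √[(1 − q)/(1 − q)³] = 1/(1 − q).

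| q (assumed) | Total loss | With post data, per arm | Complete, per arm | SE ratio, immediate contrast |
|---|---|---|---|---|
| 5% | 14% | 24.7 | 22.3 | 1.05 |
| 10% | 27% | 23.4 | 19.0 | 1.11 |
| 15% | 39% | 22.1 | 16.0 | 1.18 |

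All three rows exceed the stated 10% maximum. As an illustration, for an assumed standardised difference of 0.8 (two-sided 0.05, normal approximation), power is 77% with 23 per arm and 69% with 19.

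**Quality of life.** With only the scheduled levels (baseline, post, 6 months), two phases of 10% give √(0.9/0.81) = 1.05. With the 12-month level that the analysis text adds, and no 12-month assessment in the schedule, no participant would have a complete row.

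**Bias.** A large-sample simulation used four time levels, a true group difference in change of 0.50 SD, and drop-out after the post-training level. Effect, correlations and drop-out patterns are all assumed.

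- 10% lost at random, or the poorest 10% lost in both arms: complete cases give 0.49 to 0.50 at every level.
- The experimental arm loses its poorest responders and the control arm loses at random (10% in each, or 20% against 5%): complete cases give 0.58 to 0.63 at post under equal correlation 0.6, and 0.56 to 0.60 under autoregressive correlation 0.7. At 6 months there is essentially no bias. At 12 months there is none under equal correlation, and 0.47 to 0.42 under the autoregressive structure.
- The likelihood-based estimate stays at 0.49 to 0.51 throughout.

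**The case against.** The strongest reply is that the article never says incomplete cases will be deleted. Handling of missing values is commonly left to an analysis plan, which is not shown here, and its absence is no finding. That stands. The point is confined to the model the article does fix, and deletion is inferred from that model's default. The term mixed-model could mean a likelihood model, but pairing it with Mauchly's test speaks against this reading.

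Second, the ANOVA applies only to normally distributed data. Fall rates in 52 people may well fail the normality test and go to the Wilcoxon branch, which has no 12-month row to complete. This narrows the reach without removing the problem. Any of the three outcomes that passes still goes to the ANOVA, and the Wilcoxon branch does not handle fall rates over unequal follow-up either.

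Third, the month-8 example does not fit every outcome. For quality of life as scheduled, that participant already has every value. For falls and activity the pre-intervention level is itself unclear: calendars are described for the year after training (the Figure 1 legend says throughout), and the watch is issued in week 2.

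Fourth, the article expects little attrition and cites pilot retention. At its own 10% the cost is small. That stands, and sets the lower end of the size given here.

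A reader might go further and infer that the follow-up comparison is biased, or that all behavioural results are affected. The documents support neither. Bias needs drop-out related to outcome differently by arm, and gait and cognitive models stop at the post-training assessment.

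**Conclusion.** The concern holds for three outcome groups: fall rates (expressly secondary), physical activity and quality of life. For these, the stated method by default discards valid earlier data whenever a later level is missing. The certain effect, once anyone has a gap, is lost precision: about 5 of 52 participants and at most about 5% on the standard error at the stated 10% drop-out; about 11% on the immediate contrast under the assumed 10% per phase. Bias is a conditional risk whose size and direction depend on the drop-out pattern. The conclusion rests on reading the mixed-model ANOVA with Mauchly's test as the classical procedure, and on no imputation being planned elsewhere. Independently of this, the 12-month quality-of-life level contradicts the assessment schedule and has to be resolved.

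**What to change.** - **Activity and quality of life:** replace the ANOVA and Mauchly's test with a likelihood-based linear mixed model (REML, visit as a factor, unstructured covariance, group-by-visit contrasts) using all observed visits. Because this relies on data being missing at random, add a sensitivity analysis for non-random drop-out.
- **Falls:** compare the groups with a negative binomial model of fall counts, with log observed follow-up time as offset, so that a participant who leaves at month 8 contributes eight months.
- **Schedule:** either remove the 12-month level for quality of life from the Statistical Analyses text or add that assessment to the Figure 1 legend, Behavioral Testing and Neuropsychological Tests.

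The model changes are wording only; both procedures are available in the SPSS version named and no new data are needed. Only adding a 12-month quality-of-life assessment, if that option is chosen, would require extra collection.
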